### Sample size

The aim of the study is to establish a difference between the intervention and the control group of 20% in the proportion of subjects who are active according to the Dutch guidelines. Significance between the groups can be established with 80% (1-β) probability and a significance level of 0.05 (α). To be able to detect a difference of 20% in PA level, two groups of 50 subjects for each age group are required. Since we expect a dropout rate of 33 %, approximately 150 adolescents and 150 employees will be invited for the intervention.

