### Statistical analysis

The primary analysis will be a comparison of the change in physical activity (PA) between the intervention and control group following the "intention to treat" principle. To adjust for the dependency between observations of subjects from the same school and class or company, multilevel analysis will be performed. Intention to treat analyses will also be performed for the secondary outcomes; determinants of physical activity, quality of life, empowerment, aerobic fitness and body composition. Pre-planned subgroup analyses will be performed for adolescents and adults and separate for gender. Where appropriate, adjustments will be made for differences at baseline values. Per protocol analyses will also be carried out.

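### The gender subgroup analysis is described only as separate analyses in men and women, which do not test whether the effect differs by gender; a gender-by-treatment term in the primary model would.

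*Protocol article*

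**What the plan says.** All statements come from the protocol article.

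- **Statistical analysis, subgroups:** "Pre-planned subgroup analyses will be performed for adolescents and adults and separate for gender". The section names no gender-by-treatment term and no comparison of the two gender-specific effects. It also does not say whether gender is to be analysed across the two age groups or within each.
- **Statistical analysis, primary comparison:** "The primary analysis will be a comparison of the change in physical activity (PA) between the intervention and control group", by intention to treat.
- **Statistical analysis, model:** "To adjust for the dependency between observations of subjects from the same school and class or company, multilevel analysis will be performed". Clustering is the only reason given for using this model.
- **Sample size:** the target is a "difference between the intervention and the control group of 20% in the proportion of subjects who are active according to the Dutch guidelines", with 80% power and a significance level of 0.05. It follows that "two groups of 50 subjects for each age group are required". No number is set by gender.

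**The concern.** A gender subgroup analysis adds one question to the overall result: is the effect different in the two genders? Two separate within-gender comparisons do not answer it. Each asks only whether there is evidence of an effect in that gender, and each uses part of the sample. One gender can cross the 5% line and the other miss it when the true effect is the same in both.

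What is at stake is how the subgroup results are read. The article's Discussion says the results will inform whether the intervention should be introduced more widely. A finding that it works in one gender only could enter that decision although it reflects nothing but divided sample size. The article does not mention gender in that context, so this is a possible consequence and not a stated use.

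**Working it through.** **Inputs from the article:** 50 per arm in each age group, 80% power, significance level 0.05, 33% dropout.

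**Assumptions, because the article does not give them:** two-sided tests; an equal gender split (60/40 and 70/30 as a range); independent gender results; no allowance for clustering. The 80% power is stated for a difference in a proportion and is carried over here to the analysis of change in physical activity.

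**1. The plan's own figures.** The dropout step reproduces: 100/(1 − 0.33) = 149.3, so about 150 per age group. The 50 per arm cannot be derived from the stated inputs, because no control proportion is given. Taking the target as 20 percentage points, it is reachable, for example, with 5% versus 25% (49 per arm, two-sided, no continuity correction). The steps below start from the stated 80% power and do not need the control proportion.

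**2. Expected test statistic.** For 80% power in one age group, expected z = 1.96 + 0.84 = 2.80. With both age groups pooled, the information doubles: 2.80 × √2 = 3.96.

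**3. Power in each gender.** A gender with share s of the sample has expected z multiplied by √s, and power = Φ(expected z − 1.96), counting significance in favour of the intervention.

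- Within an age group (about 25 per arm per gender): 2.80/√2 = 1.98, so power = 0.508.
- Across both age groups (about 50 per arm per gender): 3.96/√2 = 2.80, so power = 0.80.

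**4. Chance that exactly one gender is significant when the effect is identical.** With powers a and b this is a(1 − b) + b(1 − a).

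- Within an age group: 2 × 0.508 × 0.492 = 0.50. Both are significant in 0.508² = 26%, neither in 24%.
- Across both age groups: 2 × 0.80 × 0.20 = 0.32. Both are significant in 64%, neither in 4%.

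One million simulated trials for each case gave 50.1% and 31.9%.

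**5. Unequal gender split.** Within an age group, 60/40 gives 51% and 70/30 gives 55%. Across age groups the figures are 35% and 43%.

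**6. Dependence on the true effect (equal split).**

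| True effect relative to design | Within an age group | Across age groups |
|---|---|---|
| 0 | 5% | 5% |
| 0.5 | 28% | 41% |
| 0.75 | 43% | 49% |
| 1 | 50% | 32% |
| 1.25 | 42% | 12% |
| 1.5 | 26% | 2.5% |

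**7. The same trials with an interaction test.** The statistic is (z₁ − z₂)/√2. With identical effects it is significant in 5.0% of simulated trials. A one-gender-only pattern together with a significant interaction occurs in 4.9% (within an age group) and 4.3% (across age groups), against 50% and 32% from the separate tests alone.

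**8. Power of the interaction test.** Its standard error is twice that of the overall effect. For a gender difference as large as the design effect, expected z is 2.80/2 = 1.40 within an age group and 3.96/2 = 1.98 across age groups. Power is 29% and 51%.

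**The case against.** The strongest objection is that this is a condensed article. Interaction tests and rules for reading subgroups commonly sit in a fuller plan, and silence is not exclusion. Gender-specific estimates are compatible with an interaction test, and the proposed fix reports such estimates too. This limits the point: a reader might infer that no interaction test is planned, and the article does not show that. What remains is that the article does state a form for the gender analysis, and that form does not answer the question the subgroup raises.

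Two further inferences are tempting and not supported.

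- **Extra chances of success at full alpha.** The article names one primary analysis and labels the rest as subgroup analyses. The 0.05 appears only in the Sample size section and is not assigned to subgroup tests. Nothing says that a significant result in one gender would count as success of the trial.
- **Four age-by-gender cells, each tested.** Age and gender are listed as subgroup factors, but the article does not say that they are crossed. The 50% figure is therefore conditional on a split that may not be intended, and 32% belongs to the reading across age groups.

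The objection that the 80% power refers to a proportion, while the primary analysis concerns change in physical activity, also stands. The percentages are illustrations at the design's stated power. They are not properties derived for the planned model.

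**Conclusion.** The point holds as one of analysis choice in a subgroup. As worded, the gender analysis does not test whether the effect differs by gender, and the trial is not sized for each gender. At the design effect, an identical benefit in both genders would look like a benefit in one only in about one trial in three (gender across both age groups) or one in two (gender within an age group). These figures rest on an equal gender split, two-sided 5% tests and the carried-over 80% power. The pattern is uncommon, about 5%, when there is no effect, and it becomes less frequent for effects well above design size. The primary comparison and its error rate are not affected. The change is worth making because it is specific and nearly free.

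**What to change.** Replace the wording on separate gender analyses with text such as:

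> Effect modification by gender will be examined by adding a gender-by-treatment interaction term to the primary multilevel model. The interaction estimate and its 95% confidence interval will be reported. Gender-specific effects with confidence intervals will be estimated from the same model and are exploratory. No claim of an effect in one gender only will be based on within-gender significance.

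State also whether gender is examined across both age groups or within each. If a fuller plan already contains the interaction test, bringing the article's sentence into line with it is enough.

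The cost is a few sentences and one model term, with no new data or participants. The downside is the low power of the interaction test: a non-significant result must not be read as equal effects, which is why the estimate and its interval should be reported.

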### Selection for intervention

The target group for the intervention study is relatively inactive subjects. In order to select these subjects, 300 adolescents and 300 young adults are asked to wear a PAM accelerometer during their daily activities for two weeks. The PAM display is blinded during this period. After this two weeks-period all participants are asked to fill in a short physical activity questionnaire (an adapted version of the SQUASH questionnaire; [20]). The adolescents and young adults are divided in an active and inactive group by means of a combined physical activity score. Physical activity data of the PAM and the AQUA are divided in four quartiles, stratified for educational level. The first quartile includes the most inactive subjects. For each subject the quartile-numbers of both the PAM and AQUA will be summed up. Those who are classified as 'inactive' (combined score lower than 5) will be invited for participation in the intervention study. When the combined score is five, the AQUA quartile plays a decisive role (See figure 2)

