### Intervention

The subjects classified as relatively inactive will be invited to take part in the intervention study. For the intervention study they will be required to fill in a questionnaire and to participate in physical measurements (i.e. baseline measurements). After completion of the baseline measurements the participant are randomly assigned to the intervention or the control group. Participants in the intervention group receive the PAM monitor and have access to their personal website (COACH) for a 3-month period. The participants are given written and verbal instructions and practical demonstrations on how to wear the PAM and how to use the COACH. Special attention is paid to:

1. placing the PAM on the hip;

2. connecting the docking station to the computer;

3. installing the software on the computer;

4. registering and logon to the PAM COACH website;

5. setting a PAM goal and reading the results at the COACH website.

The control group receives a single written information brochure with general recommendations and guidelines for physical activity. Telephone numbers and an e-mail-address are provided in case questions arise. At each intervention site at least one computer with PAM software is arranged.

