### Measurements

The primary outcome of the intervention study is the level of physical activity measured by questionnaire. Secondary outcomes are determinants of PA, quality of life, empowerment, aerobic fitness and body composition. A compact questionnaire is constructed to maximize the response and minimize time spent filling in the questionnaire. All measurements are performed at baseline and after 3 months of intervention. Five months after the 3 months intervention only the questionnaire is repeated.

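### Baseline adjustment of the primary change comparison is left conditional on observed baseline differences; the baseline value of the outcome should always be in the model

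*Protocol article*

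**What the plan says.** Under Statistical analysis, the protocol article defines the primary analysis this way: "The primary analysis will be a comparison of the change in physical activity (PA) between the intervention and control group", by intention to treat. A multilevel model is added for clustering: "To adjust for the dependency between observations of subjects from the same school and class or company, multilevel analysis will be performed". That model is described as a remedy for dependence within schools, classes and companies, not as adjustment for baseline activity.

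After the sentences on secondary outcomes and subgroups comes the only statement on baseline: "Where appropriate, adjustments will be made for differences at baseline values". No criterion for what is appropriate is given, and nothing commits the primary model to containing the baseline value.

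Three other places bear on the point:

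- Measurements names the outcome: "The primary outcome of the intervention study is the level of physical activity measured by questionnaire".
- Measurements also confirms that a baseline value exists for every outcome: "All measurements are performed at baseline and after 3 months of intervention".
- The Intervention section fixes the order of events: "After completion of the baseline measurements the participant are randomly assigned to the intervention or the control group".

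**The concern.** Taken together, the sentences make a change comparison the default and make adjustment depend on how the arms differ at baseline. Because allocation is random and follows baseline measurement, such differences are chance. Their presence or absence says nothing about which model is better. The case for adjusting is that baseline predicts follow-up, and that holds whether or not the arms happen to differ.

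Two things are at stake:

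1. **Precision.** A change score forces the coefficient of baseline to be 1. Estimating the coefficient does at least as well in large samples, and usually better.
2. **Discretion.** With no criterion stated, an adjusted and an unadjusted primary estimate are both available once the data are in hand.

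**Working it through.** **The plan's own figure.** Sample size gives 50 per arm in each age group, for "a difference between the intervention and the control group of 20% in the proportion of subjects who are active according to the Dutch guidelines". That calculation concerns a proportion. The article states no power for a comparison of change, so there is no figure for this analysis to reproduce. The 50 per arm serves below only as a convenient group size.

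**Inputs.**
- Equal arms of 50, randomised after baseline (Sample size, Intervention).
- Baseline/follow-up correlation rho: not given; assumed, and shown from 0.3 to 0.9.
- Standard deviation sigma equal at both times, no clustering, two-sided 5% test: assumed.

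**Variance.** For n per arm, the variance of the estimated difference is
- change score: (2/n) × 2 sigma² (1 − rho)
- baseline-adjusted (ANCOVA): about (2/n) × sigma² (1 − rho²)

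The ratio of adjusted to change score is (1 − rho²) / [2(1 − rho)] = (1 + rho)/2, which is below 1 for every rho below 1.

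The direction does not need equal standard deviations. With sigma0 at baseline and sigma1 at follow-up, the per-person variances are sigma0² + sigma1² − 2 rho sigma0 sigma1 for change and sigma1²(1 − rho²) for ANCOVA. The first minus the second is (sigma0 − rho sigma1)², which is never negative.

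**Numbers.** Suppose the effect is one that the change score detects with 80% power at 50 per arm. Adjusted power is then Φ(2.802/√ratio − 1.960). The n per arm that keeps 80% power is 50 × ratio, rounded up. The change-score group size that matches 50 adjusted is 50/ratio.

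| rho (assumed) | variance ratio | adjusted n per arm for 80% | adjusted power at 50 per arm | change-score n per arm matching 50 adjusted |
|---|---|---|---|---|
| 0.3 | 0.65 | 33 | 93.5% | 77 |
| 0.5 | 0.75 | 38 | 89.9% | 67 |
| 0.7 | 0.85 | 43 | 86.0% | 59 |
| 0.9 | 0.95 | 48 | 82.0% | 53 |

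**Does adjusting only on observed imbalance recover the gain?** The article gives no trigger, so a baseline test at p < 0.05 was taken as an example and simulated (20,000 trials per setting, 50 per arm, no clustering). At rho 0.5:

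| Analysis | SD of estimate | Power |
|---|---|---|
| Change score | 0.200 | 79% |
| Adjust only if baseline p < 0.05 | 0.194 | 80% |
| Always adjust | 0.174 | 89% |

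The first SD agrees with the formula: √(0.04 × 2 × 0.5) = 0.200. The third nearly does: √(0.04 × 0.75) = 0.173. The conditional rule recovers little of the gain.

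**Type I error**, in the same simulations at rho 0.3, 0.5 and 0.7:
- Fixed p < 0.05 trigger: 4.1% to 4.4%, so no inflation.
- Free choice of whichever analysis has the smaller p-value: 6.6% to 7.9%.

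**The case against.** The article speaks of change, not of an unadjusted change, and states no test or threshold. The sentence on baseline follows those on secondary outcomes and subgroups, so its scope is not certain. A journal article may also leave the model form and covariate list to a fuller document. The last point is right as far as it goes: the lack of a covariate list is no fault here. What remains is that the article states a rule, and the rule ties adjustment to observed differences. An analysis plan that followed it would inherit the problem.

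Change as an outcome is not itself the fault. With the baseline value in a linear model, change and follow-up give the same treatment coefficient. The only defect is the conditional wording.

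The harm is limited: the change comparison is unbiased under randomisation, a fixed trigger does not raise the type I error, and at rho 0.9 the gain is only 5% of the variance. All of this stands.

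Two stronger readings are tempting, and the article supports neither.

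- **That the trial is already short of its stated power.** Sample size gives no control proportion. For a two-sided test without continuity correction, 50 per arm fits a control rate near 5% (49 per arm). At the 18% to 31% that the Introduction reports for adolescents generally, 78 to 94 would be needed. Participants are chosen as relatively inactive, so a lower rate cannot be excluded. In any case that calculation is for a proportion, not for change.
- **That rho must be low because people were selected on the same questionnaire.** Selection for intervention says: "The adolescents and young adults are divided in an active and inactive group by means of a combined physical activity score". The score sums monitor and questionnaire quartiles, so someone in questionnaire quartile 3 and monitor quartile 1 (sum 4) is invited. The baseline questionnaire comes later and is separate, so much of any regression to the mean would fall before randomisation.

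**Conclusion.** The point holds as a matter of efficiency and prespecification, not of bias. The article makes adjustment depend on chance differences and leaves the choice of primary model open until the data are seen.

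Under equal standard deviations and no clustering, always adjusting multiplies the variance by (1 + rho)/2: from 0.65 at rho 0.3 to 0.95 at rho 0.9. These figures are illustrative, because the article gives no correlation and its model will include clustering. They also do not carry over directly to categorical secondary outcomes such as awareness or knowledge. Any inflation of type I error requires free choice between the two analyses; the undefined wording permits that but does not prescribe it. The change is worth making because it costs almost nothing.

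**What to change.** Replace the sentence on baseline differences with:

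> The multilevel model for the primary outcome, and for each secondary outcome, always includes the baseline value of that outcome as a covariate, regardless of observed imbalance between the arms.

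The primary analysis may still be described as a comparison of change. Further covariates, such as age group, sex, educational level or the monitor score from the selection period, are optional and not needed to cure this defect; if used, they must be fixed in advance. If a separate analysis plan already commits to fixed adjustment, the two texts should be brought into line.

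The cost is one sentence. No new data are needed, since every outcome is measured at baseline, and the planned multilevel model takes the covariate directly.

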## Discussion

The use of a personal activity monitor in combination with computer-directed health promotion offers a good opportunity to work interactively with large groups. This intervention method includes feedback on actual behaviour and is tailored to the individual. Since the advice given is developed interactively and takes preferences of the user into account, it is expected that physical activity can be included more easily in daily life. Additional advantages for the user of this individualized intervention are the direct feedback on the display and the flexibility of the personal COACH website system, i.e. the participants can decide when to login and monitor their stepwise progression in physical activity according to feedback information. The results of the intervention and process evaluation will contribute to the development of an effective preventive intervention and underpin the consideration whether introduction of such an intervention should be conducted at a larger scale, in the context of efficient and effective health care.
